## Abstract

**Background:**

Major depressive disorder (MDD) is a long-lasting disorder with frequent relapses that have significant effects on the patient’s family. Family psychoeducation is recognized as part of the optimal treatment for patients with psychotic disorder. A previous randomized controlled trial has found that family psychoeducation is effective in enhancing the treatment of MDD. Although MDD can easily become a chronic illness, there has been no intervention study on the families of patients with chronic depression. In the present study, we design a randomized controlled trial to examine the effectiveness of family psychoeducation in improving the mental health of relatives of patients with MDD lasting more than one year.

**Methods/Design:**

Participants are patients with MDD lasting more than one year and their relatives. Individually randomized, parallel-group trial design will be employed. Participants will be allocated to one of two treatment conditions: relatives will receive (a) family psychoeducation (four, two-hour biweekly multifamily psychoeducation sessions) plus treatment-as-usual for the patient (consultation by physicians), or (b) counseling for the family (one counseling session from a nurse) plus treatment-as-usual for the patient. The primary outcome measure will be relatives’ mental health as measured by K6 that was developed to screen for DSM-IV depressive and anxiety disorder. Additionally, the severity of depressive symptoms in patients measured by the Beck Depression Inventory–II (BDI-II) scale will be assessed. Data from the intention-to-treat sample will be analyzed 16 weeks after randomization.

**Discussion:**

This is the first study to evaluate the effectiveness of family psychoeducation for relatives of patients with MDD lasting more than one year. If this type of intervention is effective, it could be a new method of rehabilitation for patients with MDD lasting more than one year.

**Trial registration:**

Clinical Trials.gov NCT01734291 (registration date: 18 October 2012).

## Background

Major depressive disorder (MDD) is a common disorder, widely distributed throughout the population, and usually associated with substantial symptoms and role impairment. The prevalence of cases of lifetime MDD was 16.2% in the United States and 12.8% in Europe [1, 2]. The mean duration of a depressive episode was 16 weeks and 59.3% of patients with MDD lasting just one year had severe or very severe role impairment [1]. Moreover, MDD is a long-lasting illness with significant effects on the patient’s family, social life, and work life [3, 4]. Treatment failure results in a low recovery rate and frequent relapses [5]. According to studies on the naturalistic course of MDD, a prospective study in Japan showed that 10 to 20% of patients entering treatment remain chronically depressed without recovery for one or even two years [6]. Once recovered, the cumulative probability of remaining well without subthreshold symptoms was 57% at one year, 47% at two years, and 35% at five years [7].

MDD can also cause severe suffering for family members of the patient in multiple areas including a higher level of divorce [8] and severe financial strain [9]. Fadden *et al*. [10] reported that the burden on the relatives of patients with MDD included restrictions in social and leisure activities, a fall in family income, and a considerable strain on the marital relationship. Relatives of patients with depression found some of the behaviors of the patients to be difficult to bear, and the relatives had negative consequences such as grief, withdrawal, and worrying, which commonly caused problems. However, few relatives know how to deal with the difficult behavior of patients [10]. Moreover, sleep disturbance, odd ideas and/or behavior, and appetite loss in MDD patients were not seen by any relatives as being under the patient’s control, whereas nagging, grumbling, obsessionality, and worrying were seen by a varying proportion of relatives as personality attributes [10]. Therefore, the relatives felt dissatisfaction in that the patient could control those behaviors [10]. Jacob *et al*. [11] reported disruptions in the lives of close family members because of their own worrying and also because of the patient’s lack of interest in things and feelings of worthlessness. Taken together, these findings suggest that living with a patient with MDD is a source of strain and emotional distress for relatives.

Among relatives of patients with MDD, the patient’s behavior and mood disturbance and relative’s emotional distress were associated with the relatives’ mental health [12–14]. The difficultness of maintaining functioning family relationships (for example the patient may have marital problems, poorer communication, and no problem-solving skills) was associated with poorer long-term outcome for the depression [15, 16]. Rounsaville *et al*. [17] reported that a reduction in the number of marital disputes was associated with improved depressive symptoms and social functioning after eight months of individual psychotherapy in depressed female outpatients. Several studies reported that the quality of family functioning was associated with the relapse rate. The family’s expressed emotion (EE) is a good predictor of whether a patient relapses; Hooley *et al*. [18] reported that 59% of patients whose spouses had high levels of EE relapsed, although no patients living with low-EE spouses did so over a nine-month follow-up period. Although Hayhurst *et al*. [19] reported that there was no clear association between the EE of a spouse and the recurrence of depression in the patient, five studies reported that a high EE predicted a high relapse rate [18, 20–23].

These studies suggest the need for a more family-oriented approach in the treatment of MDD. However, a review conducted by Henken *et al*. [24] reported that family therapy such as behavioral intervention including psychoeducation, psychodynamic intervention, and systemic intervention for the families of patients with depression, seems to be more effective than no treatment or being placed on a waiting list. However it remains unclear how effective this intervention is in comparison with other interventions such as group intervention, individual cognitive intervention, and behavioral intervention. In spite of the lack of high-quality evidence in this field, family therapy is already a widely-used intervention for the treatment of depression [24].

Family psychoeducation is recognized as part of the optimal treatment for patients with a psychotic disorder [25, 26]. This intervention has been shown to reduce the rates of relapse and hospitalization among individuals with psychotic disorders and is recognized as an evidenced-based treatment for psychotic disorders [27]. Two randomized controlled trials have found that family psychoeducation is effective in enhancing the course of MDD [28, 29]. In a study of adolescents with MDD, patients in the group who received family psychoeducation showed greater improvements in social functioning and adolescent-parent relationship than the control group [28]. Among patients with MDD in partial or full remission, patients who were treated with the family psychoeducation had a significantly lower relapse rate than patients who were in the control group [29]. However, neither of these two trials assessed relatives’ mental health as the primary outcome. Additionally, although MDD can easily become chronic, there has been no intervention study for the families of patients with MDD lasting more than one year.

### Aims

In the present study, we perform a randomized controlled trial to examine the effectiveness of family psychoeducation in improving the mental health of the relatives of patients with MDD lasting more than one year. The hypothesis is that, compared with relatives who receive one regular counseling session from a nurse, relatives receiving family psychoeducation will show a greater improvement in mental health as measured by K6 scale at 16 weeks post-randomization.

## Methods/Design

### Design overview

This randomized controlled trial will be conducted in patients with MDD who will be allocated to one of two arms: family psychoeducation in addition to treatment-as-usual for the patients, and treatment-as-usual. Treatment-as-usual consists of consultation administered by a physician and counseling by a nurse. The primary endpoint is improvement of the mental health of patients’ relatives as measured by K6 scale at 16 weeks (Figure 1). We defined mental health as the state of health of the mind and that when the mental health of relatives was in an unhealthy state, the person suffered from mental disorder such as depressive and anxiety disorder.

**Figure 1 Fig1:**
[figure not shown]
**Participant flow diagram.** K6, J-ZBI_8; The Japanese version of the Zarit Burden Interview short version, FAS; The Japanese version of the Family Attitude Scale, BDI-II; Beck Depression Inventory-II, SF-36; The Medical Outcomes Study 36-item short form health survey (SF-36) version 2, FAD; The Japanese version of the Family Assessment Device.

### Participants: inclusion and exclusion criteria

The target population will be patients with MDD lasting more than one year and their relatives (fathers, mothers, husbands, wives, daughters, and sons of patients). Inclusion criteria will be: the patient meets the criteria for MDD according to the DSM-IV (Diagnostic and Statistical Manual of Mental Disorder 4^th^ edn) based on the consensus rating by psychiatrists (who have more than five years’ experience as a physician and more than two years’ experience as a psychiatrist) in charge without using a structured interview; the patient receives antidepressant therapy; the patient had the first episode of MDD more than one year prior; the patient currently fulfills the diagnostic threshold for major depressive episode or partial remission; the patient and their family member(s) are aged between 18 and 85 years; the patient lives with his or her family at the time of participating in this study and is expected to live with his or her family during the investigation period. Exclusion criteria will be: patients who undergo electroconvulsive therapy (ECT) during the investigation period and patients who are at serious suicidal risk.

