### Randomization

Participants will be randomly allocated to one of the two groups with equal probability. This random assignment will be made in a 1:1 ratio. An independent statistician will generate the random allocation sequences by a computer using minimization [30], and stratify the relatives according to the severity of mental state (K6 score of 5 or more, or less than 5). Allocation sequences will be kept centrally and the allocation will be provided by facsimile to us. The randomization schedule is not available to anyone except the statistician.

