#### Control group

The patients in both the intervention and control groups will receive standard outpatient or inpatient treatment administered by physicians. Outpatient treatment consists of evaluation of psychiatric symptoms, antidepressant pharmacotherapy, and supportive psychotherapy on a bi-weekly or-four-weekly basis. Inpatient treatment consists of sufficient rest for the patient, evaluation of psychiatric symptoms, antidepressant pharmacotherapy, and supportive psychotherapy. All of the participants will receive some case management. Family treatment in the control group consists of one counseling session administered by a nurse. This counseling consists of listening to any issues or problems and providing any information that is ask for. The information requested is usually regarding their communication, relapses, and how to take their drugs. We selected this counseling treatment as the control group’s treatment, because active listening to relatives’ suffering and giving information on recuperation from nurses are within the scope of treatment-as-usual. The one session of counseling by a nurse will last 45 minutes.

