### Statistical analysis

Statistical analyses will be performed using SPSS 19 J for Windows. Descriptive data analysis will be conducted by calculating mean scores and standard deviation. All analyses will be based on the intent-to-treat model. We will use analysis of covariance at 16 weeks if there is no missing data at that time. If missing data is observed, we will use the maximum likelihood mixed model which accounts for missing data, provided that the data are missing at random, conditional on the covariates and the baseline values of the outcome. *P* <0.05 will be set to test the null hypothesis.

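### The primary model names no patient-level covariate; prespecifying the patient's baseline BDI-II would buy precision almost free in a small trial that mixes full-episode and partial-remission patients

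*Protocol article*

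**What the plan says.** All references are to the protocol article.

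- **Eligibility** (Participants: inclusion and exclusion criteria): a family qualifies if "the patient currently fulfills the diagnostic threshold for major depressive episode or partial remission". The requirement of more than one year runs from the patient's first episode, so it does not narrow the current state. The Control group section adds that patients in both arms "will receive standard outpatient or inpatient treatment administered by physicians".
- **Link to the outcome** (Background): earlier studies found that "the patient’s behavior and mood disturbance and relative’s emotional distress were associated with the relatives’ mental health".
- **Allocation** (Randomization): "This random assignment will be made in a 1:1 ratio", by minimization. The statistician will "stratify the relatives according to the severity of mental state (K6 score of 5 or more, or less than 5"). No patient characteristic is named.
- **Analysis** (Statistical analysis): "We will use analysis of covariance at 16 weeks if there is no missing data at that time". With missing data, a maximum likelihood mixed model is used instead. Its missing-at-random condition refers to covariates, which are not listed, and to the outcome's baseline value.
- **Data available**: patients and relatives both complete Assessment I before randomization (Procedure), and BDI-II is a patient outcome (Secondary outcomes in patients).

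**The concern.** Two relatives with the same K6 at entry may follow different courses over 16 weeks if one lives with a patient in a current episode and the other with a patient already in partial remission. Baseline K6 captures the relative's distress at entry, but not necessarily its expected course. If patient state carries prognostic information beyond baseline K6, two things follow in a trial of about 30 families per arm. The arms may differ by chance in the mix of patient states, which shifts the estimated difference in K6 in one direction or the other. And even with a perfect balance, the spread due to patient state stays in the residual variance, although a measure of it should already be in hand at baseline.

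Timing also matters. A covariate chosen after an imbalance has been seen is open to challenge; the same covariate named in advance is not.

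**Working it through.** **Inputs from the documents** (Sample size and statistical power): K6 change of 4.5 versus 2, SD 2.5, two-sided 5% level, power 0.90, 23 evaluable and 30 recruited per arm, 20% dropout.

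**Assumptions, because the documents give no figure:** the true share *q* of patients in a full episode (30% or 50%); the effect *g* of patient state on K6 change (1 to 3 points); the partial correlation *r* of the patient's baseline BDI-II with 16-week K6 given baseline K6 (0.1 to 0.4). One relative per patient is assumed throughout.

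**Step 1: the plan's own figure.** The difference is 4.5 − 2 = 2.5, so d = 2.5/2.5 = 1.0. The normal formula gives n = 2 × (1.960 + 1.282)² × (SD/difference)² = 21.0, that is 22 per arm. The t-based calculation gives 22.02, that is 23 per arm, with power 0.912 at 23. So the stated 23 reproduces. Dropout: 23/0.8 = 28.75, that is 29; the plan recruits 30.

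**Step 2: chance imbalance in patient state.** Treat the numbers in a full episode as two independent binomials (n, q) and sum exactly the probability that the two proportions differ by 0.20 or more.

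| n per arm | q = 0.3 | q = 0.5 |
|---|---|---|
| 30 | 0.120 | 0.155 |
| 23 | 0.146 | 0.184 |

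Minimization on the relative's K6 would lower these a little if K6 and patient state go together.

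**Step 3: what that imbalance does to K6.** The shift in the arm difference is 0.20 × g, that is 0.2 to 0.6 points for g = 1 to 3. Against the planned 2.5 this is 8 to 24%. The standard error at 23 per arm is 2.5 × √(2/23) = 0.74, so the shift is about 0.3 to 0.8 standard errors. At q = 0.5 the state effect explains g² × 0.25/2.5² of the variance: 4%, 16% and 36% for g = 1, 2 and 3, which corresponds to r = 0.2, 0.4 and 0.6. So g = 3 lies outside the range of r assumed here; within that range the shift is at most about 0.4 points.

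**Step 4: what adjustment buys.** Residual variance is multiplied by 1 − r², and the equivalent gain in families is 1/(1 − r²). Power is t-based at 23 per arm for a difference of 2.5, with residual SD = 2.5 × √(1 − r²). This takes 2.5 as the SD before BDI-II is added and does not charge the one degree of freedom.

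| r | 1 − r² | Residual SD | 1/(1 − r²) | Power at 23 per arm |
|---|---|---|---|---|
| none | 1.00 | 2.50 | 1.00 | 0.912 |
| 0.1 | 0.99 | 2.49 | 1.01 | 0.915 |
| 0.2 | 0.96 | 2.45 | 1.04 | 0.923 |
| 0.3 | 0.91 | 2.38 | 1.10 | 0.935 |
| 0.4 | 0.84 | 2.29 | 1.19 | 0.951 |

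**The case against.** The strongest reply is that nothing here is an error. Randomization makes the unadjusted comparison valid, and its standard error already allows for chance imbalance of this kind, which can favour either arm. Power at the planned size exceeds 0.90 without the covariate. Stratifying on the relative's K6, and any adjustment for baseline K6, already absorb whatever part of the patient's state shows in the relative's distress at entry. Mixed enrolment suits the effectiveness aim set out in the Discussion. And an article may leave its covariate list to a fuller document. All of this stands. It limits the point to an improvement in precision; it does not remove it, because the covariate costs so little.

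Four stronger readings are tempting, and the document does not support them:

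- *That the analysis ignores patient severity.* The Statistical analysis section mentions covariates without listing them. Adjustment is unspecified, not excluded.
- *That the protocol treats patient state as a cause of the relatives' K6.* The Background reports an association with behavior and mood disturbance. It makes no causal claim and does not compare a full episode with partial remission.
- *That episodes will typically resolve just in time for the endpoint.* The Background does say "The mean duration of a depressive episode was 16 weeks", the same length as the primary follow-up. But that figure describes MDD in general, whereas these patients had their first episode more than a year ago, are on antidepressants and enter at an unknown point in an episode. The same section reports that 10 to 20% of treated patients stay depressed for one or even two years.
- *That patient state should now become a second minimization factor.* The Trial status section says randomization began in October 2012. A new factor would change the allocation procedure mid-trial, and a clinician-rated state would not match a self-reported BDI-II in the model. The case for the covariate does not depend on it.

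**Conclusion.** The point holds as a modest, inexpensive improvement. Both patient states are eligible, the only balancing factor named is the relative's K6, and no text commits to adjusting for the patient's condition. The consequence is chance imbalance and some lost precision, not bias, and the sample size does not need to change.

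The gain is negligible at the low end of the assumed correlations and useful at the high end. It would matter most if the true effect is smaller than the planned 2.5 points, since a chance shift of a few tenths of a K6 point then weighs more. All figures on imbalance, state effect and gain rest on assumed values; only the sample size inputs come from the document. That BDI-II is recorded for patients at Assessment I is inferred from the Procedure and outcome sections, because the flow diagram is not shown.

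**What to change.** In the Statistical analysis section, or in the analysis plan if one exists, name the covariates of the 16-week primary K6 model as the relative's baseline K6 and the patient's baseline BDI-II, both as continuous values. Apply the same list to the analysis of covariance and to the mixed model. Say explicitly that it is the patient's BDI-II, because the relatives complete that scale too. Date the change before outcome data are compared by arm; the trial is still recruiting, so this is possible. If a fuller document already lists this covariate, no change is needed.

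The cost is one degree of freedom and one simple rule, fixed in advance and blind to arm, for a missing baseline BDI-II (for example, the mean over both arms combined), so that no relative is lost from the primary analysis because a patient's questionnaire is absent. No new data are collected, and the minimization factors stay as they are.

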### Procedure

This study was approved by the Ethics Review Committee of Nagoya City University Graduate School of Medicine (reference number 679). All participants will provide written informed consent after the purpose and procedures of the study are explained. This study is registered at ClinicalTrials.gov under number NCT01734291. We will provide eligible patients with an ID number and then ask patients and their relatives to provide informed consent and complete a baseline assessment (Assessment I). After providing informed consent and completing the baseline assessment, participants will be randomized. Assessment will occur at baseline, before randomization, and at 8, 16, and 32.

### Randomization

Participants will be randomly allocated to one of the two groups with equal probability. This random assignment will be made in a 1:1 ratio. An independent statistician will generate the random allocation sequences by a computer using minimization [30], and stratify the relatives according to the severity of mental state (K6 score of 5 or more, or less than 5). Allocation sequences will be kept centrally and the allocation will be provided by facsimile to us. The randomization schedule is not available to anyone except the statistician.

### Treatment

#### Multifamily psychoeducation

The family intervention program, which we call ‘multifamily psychoeducation’, is based on the McFarlane Model [31], the Evidence-Based Practices Toolkit for Family Psycho-Education [32], and the standard model of the Japanese Network of Psychoeducation and Family Support Program (JNPF) [33]. The multifamily psychoeducational program will consist of four sessions. Each of the four multifamily psychoeducational program groups will consist of the relatives of approximately four patients. The staff will consist of one or two psychiatrists, one or two nurses, one pharmacologist, and one social worker. The teaching materials for the relatives of the patients are a videotape produced by the Department of Neuropsychiatry, Kochi Medical School [34], including the videotaped interview of the experience of a patient with MDD, an explanation of the cause of MDD using computer graphics images of synapses and neurotransmitters, and a booklet developed by our department. At the first session we will give the participants information on the causes and symptoms of major depression, at the second session we will provide information on drug treatment, at the third session we will provide information on community resources, and at the fourth session we will provide guidelines for families caring for patients. After the lecture in each session, we will provide supportive group therapy focusing on problem-solving skills for approximately 90 minutes. In the group therapy sessions, the participants will be encouraged to give a narrative of their subjective experience in taking care of the MDD patient. Each session will last approximately two hours. The groups will meet once every two weeks over the course of six weeks.

